**Methods:**

A mixed-method, randomised controlled trial with 122 caregivers of PwD will be conducted. Participants will be assigned to either the Inlife social support intervention or a waiting-list control group. After 16 weeks, the control group will obtain access to the Inlife environment. Data will be collected at baseline (T_0_) and at 8-week (T_1_), 16-week (T_2_) and 42-week follow up (T_3_). The 16-week follow-up assessment (T_2_) is the primary endpoint to evaluate the results on the primary and secondary outcomes, measured by self-reported questionnaires. The primary outcomes include feelings of caregiver competence and perceived social support. The secondary outcomes include received support, feelings of loneliness, psychological complaints (e.g., anxiety, stress), and quality of life. A process evaluation, including semi-structured interviews, will be conducted to examine the internal and external validity of the intervention.

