## Methods/design

An RCT design will be used to compare a waiting-list control group with an intervention group. Self-reported data will be collected pre-intervention (T_0_) and at 8-week (T_1_) and 16-week follow up (T_2_). The 16-week follow-up assessment serves as a primary endpoint to compare group effects. After the initial 16-week study period, the participants in the waiting-list control group can start using the Inlife platform, whereas caregivers in the intervention group are free to continue using the platform. Furthermore, a long-term follow-up measurement is scheduled for 42 weeks (T_3_) after baseline. See Fig. 1 for the flow diagram. This paper follows the Standard Protocol Items: Recommendations for Interventional Trials (SPIRIT) guidelines, which can be found in Additional file 1.

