### Sample size

The sample size was determined based on previous intervention studies of caregivers of PwD with the Short Sense of Competence Questionnaire (SSCQ) as an outcome measure [16, 36], using repeated measures and interaction within and between variables with a mean effect size of 0.5. In accordance with the following assumptions: alpha 0.05 and power 80%, we aim to include 102 primary caregivers (51 participants per group). Allowing for a 20% loss to follow up, we aim to enrol 122 caregivers.

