### Statistical analysis

#### Primary and secondary outcome measures

All analyses will be performed according to the intention-to-treat principle, using IBM SPSS Statistics (IBM Corp. Released 2016. IBM SPSS Statistics for Macintosh, Version 24.0. Armonk, NY: IBM Corp).

Prior to the main analysis, data will be examined for missing values, outliers and normality. To investigate whether randomisation was successful, potential differences in the baseline characteristics of the intervention and control groups will be determined using either the *t* test for the continuous variables or the chi squared (X^2^) test for the categorical variables. In the case of missing values, we will examine whether they are missing completely at random (MCAR). If the variables are MCAR, based on a comparison between the baseline characteristics of the study completers and the participants with missing values (no *P* value < .05), list-wise deletion will be applied, whereas when the missing values are not at random, we will apply a multiple imputation strategy [37].

To test the first hypothesis examining the differences in the outcome variables of the intervention group and waiting-list control group, analysis of covariance (ANCOVA) will be performed, with the outcomes of the T_2_ assessment (i.e., measured at 16 weeks, after this period the waiting-list control group can start with Inlife). The outcomes assessed at the T_2_ follow up will be included in the model as dependent variables and groups as between-subject variables. Potential baseline differences between the treatment arms will be included as covariates, if necessary. Each outcome measured will be assessed as a dependent variable in separate analyses.

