To test the changes in the primary and secondary outcome measures over the total study period, data from the intervention group and waiting-list control group will be analysed using a linear mixed model (LMM). The LMM will estimate the fixed effects of the regression slopes representing the changes during the intervals (T_0_-T_1_) and (T_1_-T_2_) in the intervention only and waiting-list control group and after the (T_2_-T_3_) follow up. This process enables a comparison of the rate of change in the caregivers who did not receive the intervention compared to the caregivers who received the intervention (T_0_-T_2_), and it provides insight into whether the potential effects on the outcome variables will be sustained by evaluating the rate of change from the 16-week follow up to the 42-week follow up (T_2_-T_3,_ intervention group only). Furthermore, LMM accounts for the fact that the data are correlated through nesting in individuals. Potential missing values are handled efficiently under the missing at random (MAR) assumption, using maximum likelihood estimates for the missing observations; hence, it is suitable for intention-to-treat analysis. Therefore, variables known to predict missing values will be included in the LMM analyses [38]. Intervals will be entered as categorical variables, using three dummies. The best model fit of the models with random intercept (at the participant level) and with random intercept and random slope (at interval level) will be compared with likelihood ratio tests. All tests will be two-tailed, with an alpha level of 0.05.

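### Two unranked primary outcomes are each tested at two-sided 0.05 with no success rule, so the family-wise error is about 8–10% if either one may carry the claim

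*Protocol article*

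**What the plan says.** All references are to the protocol article.

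- **Outcomes.** Abstract, Methods: "The primary outcomes include feelings of caregiver competence and perceived social support". The section Primary outcome measures describes SSCQ and MSPSS one after the other and does not rank them.
- **Time point.** Methods/design: "The 16-week follow-up assessment serves as a primary endpoint to compare group effects".
- **Main test.** Statistical analysis, Primary and secondary outcome measures: the first hypothesis is tested by ANCOVA on the T2 scores, and "Each outcome measured will be assessed as a dependent variable in separate analyses".
- **Second model.** The same section fits an LMM to the primary and secondary outcomes over the whole study. One of its stated uses is to compare the rate of change between arms from T0 to T2.
- **Error level.** The section ends: "All tests will be two-tailed, with an alpha level of 0.05".
- **Sample size.** The Sample size section rests on earlier studies "with the Short Sense of Competence Questionnaire (SSCQ) as an outcome measure", "with a mean effect size of 0.5", with an undivided alpha of 0.05, 80% power and 51 per group. It does not say that SSCQ is to be tested first or is the only confirmatory outcome.

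**The concern.** Two primary tests, each at the full 0.05, give two chances of a false positive. A single trial-wide error rate of 5% then holds only if the plan says how the two results combine: in order, with a shared alpha, or with both required. The article says none of these. If only one outcome reaches significance, nothing written in advance settles whether the trial has succeeded, and the choice would be made with the results in view. The overlapping T0–T2 comparison in the LMM, at the same 0.05, adds a further opportunity on each outcome.

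**Working it through.** **Inputs from the article.** Two primary outcomes; one primary time point (T2); a separate ANCOVA for each; two-sided 0.05 for every test; effect size 0.5; 51 per group.

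**Input not in the article.** The correlation r between the two test statistics. It is assumed, and a range is shown.

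**Step 1: the plan's own figure.** For a difference d = 0.5 in SD units, the normal formula is n = 2(z_α + z_β)²/d² per group.
- Two-sided 0.05, 80% power: 2(1.960 + 0.842)²/0.25 = 62.8, so 63 (64 by the t test).
- One-sided 0.05: 50 by the normal formula and 51 by the t test (power 80.6%).
- Two-sided 0.05 gives 51 if a baseline correlation of about 0.44 is assumed, since the variance is then multiplied by 1 − 0.44².

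The article mentions repeated measures but gives no correlation, so the route to 51 is not certain. Each route uses an alpha of 0.05 that is not divided between two outcomes, and that is what matters here.

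**Step 2: error across two tests with no true effect on either outcome.**
- Independent: 1 − (1 − 0.05)² = 0.0975.
- Correlated: P(|Z1| > 1.96 or |Z2| > 1.96) from the bivariate normal distribution.
- In favour of Inlife only: P(Z1 > 1.96 or Z2 > 1.96). When independent this is 1 − 0.975² = 0.0494.

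| r | Any false positive, two-sided | False positive in favour of Inlife |
|---|---|---|
| 0 | 9.75% | 4.9% |
| 0.3 | 9.5% | 4.8% |
| 0.5 | 9.1% | 4.5% |
| 0.7 | 8.3% | 4.2% |
| 0.75 | 8.1% | 4.0% |
| 0.8 | 7.8% | 3.9% |
| 0.9 | 7.0% | 3.5% |

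A single test has 5% and 2.5% respectively. The two-sided figure lies between 8% and 10% for r from 0 to about 0.75.

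**Step 3: what control would cost in power.** Two-group t test, d = 0.5, 51 per group. With a baseline covariate at an assumed correlation of 0.5, the effective difference is 0.5/√(1 − 0.5²) = 0.577.

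| Two-sided alpha | No baseline adjustment | Baseline correlation 0.5 (assumed) |
|---|---|---|
| 0.05 | 71% | 82% |
| 0.025 | 60% | 74% |

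A fixed sequence tests its first outcome at 0.05, so that outcome stays on the upper row. Under Holm, the smaller p value is judged at 0.025 (lower row), and the other at 0.05 if the first passes.

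**The case against.** **The success rule is inferred.** The inflation arises only if either outcome alone can carry the claim, and the article never says so. The first objective in the Background, and the expectation stated in the Discussion, join social support and competence with *and*. If both had to be significant, there would be no inflation, only a loss of power. If each outcome were claimed strictly for itself, each claim would carry its own 5%. This stands, and it is why the figures are conditional. It does not remove the point: the article states no both-must-succeed rule either, and its sample size is not built for joint success.

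**The size can be overstated.** A reader might infer that the chance of falsely declaring Inlife effective is 8–10%. That range also counts false results against Inlife. The rate in its favour is about half, though still nearly double the 2.5% of one test.

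**The choice of model is mostly settled.** A reader might infer that success in either model would do. The documents do not support that: the ANCOVA on T2 scores is assigned to the first hypothesis, T2 is the primary endpoint, and the LMM is introduced for change over the whole study and for maintenance. What remains is the LMM's T0–T2 comparison of arms at the same alpha, which is not labelled supportive.

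**This may belong in the analysis plan.** Order and gatekeeping are often placed there, and 0.05 per test is compatible with a fixed sequence. But the article is not merely silent: it fixes 0.05 for all tests in separate analyses. Followed as written, that leaves the two-outcome error rate uncontrolled, and a later division of alpha would contradict it.

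**Conclusion.** The point holds in conditional form. Two unranked primary outcomes are each tested at two-sided 0.05, with no order, alpha split or joint requirement. If either may be read as effectiveness, the family-wise two-sided error is about 8–10% for an assumed correlation of 0 to 0.75. In favour of Inlife alone it is about 4.2–4.9% for correlations of 0.7 down to 0, against 2.5%. These figures assume no true effect on either outcome and count only the two ANCOVAs; the LMM's overlapping comparison can only raise them if it too is allowed to count. The article does not establish that either outcome suffices, so it would be wrong to report the inflation as the trial's written rule. It is a should-fix: the rule is missing where it decides the main conclusion, but supplying it leaves the trial's conduct untouched.

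**What to change.** Before analysis, state the success rule for the two primary outcomes. Either of these controls the error at 5%:

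1. **Fixed sequence.** Test SSCQ at T2, the outcome the trial was sized on, at two-sided 0.05. Test MSPSS at 0.05 only if SSCQ is significant. *Cost:* SSCQ loses no power, but MSPSS cannot be claimed as confirmatory if SSCQ is not significant.
2. **Holm across the two.** Judge the smaller p value at 0.025 and, if it passes, the other at 0.05. *Cost:* neither outcome depends on a preset order, but at 51 per group the power for a single outcome tested at 0.025 is 60% rather than 71% unadjusted, or 74% rather than 82% with the assumed baseline correlation of 0.5. The sentence fixing 0.05 for all tests would also need amending.

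In the same place, state that the T2 ANCOVA is confirmatory and that the LMM and all secondary outcomes are supportive. This takes a sentence or two, and neither the sample size nor data collection changes. The Trial status section says recruitment is under way, so the rule can still be set before the results are known.

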### Semi-structured interviews and process evaluation

Data obtained from the qualitative semi-structured interviews (with a subsample of approximately 10 participants) will be transcribed verbatim. Two independent researchers will conduct inductive and deductive content analyses of the transcribed interviews in ATLAS.ti. Text fragments will be assigned codes, which will be organised into categories. Then, the categories will be merged into common themes in a consensus meeting with a third independent researcher.

All participants will rate their opinions regarding the usability and user-friendliness of Inlife on the PPQ. These scores will be analysed through descriptive statistics. Additionally, explorative analyses of the research database will be performed to summarise the response rates, reasons for participation, researchers’ notes of user experiences with Inlife and findings regarding sampling quality and intervention quality.

## Discussion

In this paper, we outlined the design of a randomised waiting-list controlled trial to evaluate the effectiveness and process of Inlife, an online social support platform for caregivers of PwD to improve social support, feelings of caregiver competence and positive interaction. The development of Inlife was based on the Medical Research Council (MRC) framework and tested in a feasibility study [12]. The Inlife intervention is specifically developed with potential users, and it is unique because it facilitates social support for the primary caregiver and PwD in separate care circles, thereby providing different functionalities and privileges to all involved network members.

As suggested by the MRC framework, we considered the factors that can influence implementation by integrating a process evaluation in our study design. The process evaluation will facilitate understanding about the delivery and quality of the intervention and provides insight into the contextual, personal and situational factors influencing the intervention effectiveness in a real-world setting [11, 39]. We expect the intervention to be successfully implemented because Inlife is designed together with potential users, and it will be made available by both community services and online services at the regional and national levels.

Using a mixed-method design, our study will provide valuable insight into the real-life usability and effectiveness of the Inlife intervention. Previous studies have shown that the measures used in intervention studies often do not fit the targets addressed by the intervention [40], therefore, we used a custom interpersonal relationship scale to measure positive interactions, specifically within the dementia care network. Additionally, the semi-structured interviews may provide insight into the possible barriers to and facilitators of implementation. This information will be essential not only to improve the Inlife platform but also to implement the Inlife intervention on a broader scale in clinical practice. Moreover, our study findings will provide recommendations for future research into online interventions for caregivers, as these studies are expected to increase due to the increase in computer literacy and education level of future generations being faced with growing numbers of PwD [11].

In conclusion, the results of this study will add to the knowledge base of the usability and effectiveness of e-health interventions to support caregivers of PwD. We expect that Inlife will effectively increase caregiver social support and feelings of competence, and might aid in the positive interactions within the dementia caregiver network. This study will also provide valuable insights for policy makers, clinicians and researchers into the challenges in the usability and implementation of online social support interventions in the field of dementia care.

Given the promising benefits of technology and online support [9, 11], Inlife might be a valuable social support resource that can be used in routine dementia care. Where the focus is shifting towards improving social health and living well with dementia [41, 42] by maintaining independence and engagement in social activities and daily life for PwD and their caregivers.

### Trial status

The recruitment of participants for this study began in June 2016, and currently, caregivers of PwD are being recruited.

## Abbreviations

CarerQol: Care Related Quality of Life scale
CONSORT: Consolidated Standards of Reporting Trials
EQ-5D: Euroqol-5D
HADS: Hospital and Anxiety Stress Scale
ICECAP*-*O: Investigating Choice Experiments for the Preferences of Older People Capability Measure for Older People
LS: Loneliness Scale
LSNS*-*6: Lubben Social Network Scale
MRC: Medical Research Council
MSPSS: Multidimensional Scale of Perceived Support
PPQ: Programme participation questionnaire
PSS: Perceived Stress Scale
PwD: People with dementia
RCT: Randomised controlled trial
SPIRIT: Standard Protocol Items: Recommendations for Interventional Trials
SSCQ: Short Sense of Competence Questionnaire
SSL12*-*I: Social Support List 12-Interactions
VAS: visual analogue scale
